## Methods

### Research Design

We will adopt a pragmatic study design to systematically assess implementation strategies to increase breast and cervical cancer screenings and evaluate the sustainability of the strategies. Due to multiple multilevel barriers associated with the extremely low screening uptake in Kenya, we created the C3Link multicomponent strategies targeted at barriers at the individual, interpersonal, and structural levels. These strategies are guided by the COM-B change model [3] as described in the Introduction section.

### Selection of Study Counties and Facilities

The C3Link trial will be conducted in 3 counties in Kenya: Machakos, Nakuru, and Nyeri. We will target populations inhabiting fixed dwellings in neighborhoods that are within breast and cervical cancer screening clinic catchment areas. Communities will be within a 30-minute walking radius from the clinics and a 90-minute travel radius from mammography facilities.

In consultation with key stakeholders in cancer control, we purposively selected the 3 representative counties. In each county, we identified 3 primary care clinics that offer breast and cervical cancer screenings. Each of the study clinics have more than 3 similar neighborhoods (community health units) attached to it. Our goal was to select distinct communities that were not contiguous to avoid cross-contamination.

### Implementation Strategies

Women enrolled in the C3Link Core and Plus communities will receive a package of strategies delivered by study CHWs in the community setting. CHWs are community members who receive standardized training to collect data on demographics and health needs in their communities while supporting management of minor ailments and making referrals for other ailments. Each CHW supports up to 100 households. In Kenya, they are referred to as community health promoters.

CHWs play an important role in addressing individual and interpersonal barriers to improve knowledge and encourage women to seek medical care. In order to optimize available resources, we will adopt a tiered process through which only women who require multiple strategies are offered them. We will include a C3Link Core group receiving education sessions only where CHWs deliver group education sessions to women and their support persons, a C3Link Plus group will receive the C3Link Core group education sessions and later add on individual evidence-based strategies that increase in resource intensity in a sequential order, targeting women who remain unscreened at 1-month intervals, and a third group receiving enhanced usual care (ie, distribution of flyers in addition to usual care).

At the clinic level, C3Link Core and Plus strategies will use practice facilitation in clinics to foster team-based care with CHWs embedded within the clinic teams to build optimal community linkages and communication channels. CHWs serving as team members in the clinic setting can cocreate optimal processes in screening clinics to coordinate the return of test results to women and support completion of follow-up recommendations. We will provide education to health care providers to improve communication and reduce any stigmatizing behaviors. Through the practice facilitation process, we will implement a learning collaborative that offers peer-to-peer consultations to improve screening capacity.

The enhanced standard-of-care communities will not have any CHWs. During enrollment, we will distribute campaign flyers provided by the National Cancer Institute of Kenya. Women who visit clinics may benefit from quality improvement processes. Table 1 provides details on the activities and goals of strategies during each phase of this study.

**Table 1. T1:** Training and delivery of the multicomponent strategies.

Setting—Goal	C3Link^a^ Core and C3Link Plus	Enhanced standard of care
Preimplementation phase for planning (6 months)		
Community—train CHWs^b^	13 basic modules plus 6 modules of study-specific content	No study CHWs
Clinic—strengthen quality, referrals, and provider interactions	Readiness assessment; standard procedures, diagnosis triage; training on high-quality screening and documentation	Readiness assessment; standard procedures, diagnosis triage; training on high-quality screening and documentation
Intervention phase to test multicomponent strategies (24 months implementation and follow-up)		
Community— Increase women’s knowledge, self-efficacy, care-seeking behavior, and social support (reduce stigma) Deliver individual strategies that increase in intensity to women who need additional support (C3Link Plus only)	C3Link CHW-led education sessions (each community): Three-weekly women’s club meetings with education modules Six group sessions for family members or support persons	Awareness campaign in the community using flyers developed and provided by the National Cancer Institute of Kenya
Community— Increase women’s knowledge, self-efficacy, care-seeking behavior, and social support (reduce stigma) Deliver individual strategies that increase in intensity to women who need additional support (C3Link Plus only)	C3Link Plus only—focus on care-seeking behavior: Level 1: women not screened at 9 months will receive one-on-one education, level 2: women not screened at 10 months will receive individual counseling through motivational interviewing, and level 3: women not screened at 11 months will receive navigation to address barriers	Awareness campaign in the community using flyers developed and provided by the National Cancer Institute of Kenya
Clinic— Embed study CHWs so that, with their support, results and referrals are conveyed Improve the quality of screening	Practice facilitation with community linkages (each clinic) Monthly case review meetings with study CHWs and PDSA^c^ cycles with clinic teams led by clinic champions	Those who visit clinics may benefit from improvements, but there are no community–clinic linkages with CHWs
Maintenance phase to test reduced level of support (additional 24 months for a total of 36 months of follow-up)		
Community—provide support to maintain behavior change	Quarterly women’s club meetings Two group sessions for family members or support persons	Awareness campaign continues
Clinic—further embed team-based care and linkages	Quarterly meetings with study CHWs and PDSA cycles	Individuals may benefit from quality improvements at visits

a CHW: community health worker.

b C3Link: cancer community–clinic linkage.

c PDSA: Plan-Do-Study-Act is a rapid-cycle improvement process.

### C3Link Community Implementation

We will recruit C3Link study CHWs (women) from the C3Link communities in the preimplementation phase using the same process used by the Kenyan counties. We will assign 1 study CHW in each community selected to implement C3Link Core or Plus strategies. To ensure continuity, the study CHW will have the primary responsibility for the implementation and will be supported by county CHWs who will step in if required. The study CHWs will receive a 1-week training session that will be delivered by our study team. They will receive training on 13 standardized topics, including practical experience providing services in the community. The study-specific topics will include breast and cervical cancer screening, review of the content of the education sessions for women and support persons, and facilitation of group education sessions. The C3Link Plus CHWs will later receive training on the facilitation of one-on-one education sessions, motivational interviewing techniques, and delivery of navigation services. The C3Link study-specific training content will be prepared by updating training materials (based on published toolkits) [49-53] developed by the team for ongoing studies (R01CA200845 and UH3HD096908). Study CHWs will also be trained in the use of the C3Link CHW tracking tool, in which they will be documenting all interactions with the participants.

### CHW–Led Group Education Sessions for Women and Family Members

The education modules for women will be based on training materials and graphics developed by the Kenyan MOH for the pilot studies conducted in Nyeri and Meru counties [14,31]. Modules related to stigma and decision-making will be drawn from toolkits previously used in the Kenyan setting and available in both English and Kiswahili [54,55]. We will convene focus groups of 10 participants in each county (outside the study communities) to pretest the education modules for comprehension, appropriateness, and understandability.

The education modules will include 12 modules for women packaged into 2-hour women’s club or support person sessions. For women, the core content will be delivered during the first 9 months of the intervention phase, and additional content will be offered for the remaining 12 months. The 6 group education sessions planned for caregivers will cover the core content and will take place every other 3 weeks during the first 9 months of the intervention phase. During the maintenance phase, the reduced number of education sessions for women and caregivers will be drawn from the additional content that is available and tailored to the needs articulated by participants.

### C3Link Plus Sequence of Personalized Strategies

A sequence of individual strategies will be provided by study CHWs to women who remain unscreened at the 9-month follow-up. Women will be considered unscreened if they do not initiate any screenings or complete only one of the recommended screenings (breast or cervical). First, at 9 months, one-on-one education to reinforce concepts from group sessions and address specific misconceptions or myths expressed by the women. Second, those who remain unscreened at 10 months will receive motivational interviewing. Third, those who remain unscreened at 11 months will receive navigation to address any remaining barriers.

### Women Requiring Follow-Up Procedures

Study CHWs will inform participants within communities when HPV test results become available. During the HPV test results collection and breast cancer screening visit, providers will inform participants who require diagnostic procedures or treatment. Otherwise, for women who will not go to the clinics for their results and/or breast cancer screening, study CHWs will contact them after 2 weeks—encouraging them to visit their respective clinics, and providing navigation to support completion of required tests or treatments as needed. As in prior pilot studies, these procedures will be financed through Kenya’s Social Health Authority with supplementation from this study when necessary.

### C3Link Clinic Setting

During the preimplementation phase, we will conduct a readiness assessment to deliver breast and cervical cancer screening at the 9 participating clinics using the World Health Organization’s Service Availability and Readiness Assessment [56,57], which has been previously used to evaluate cancer screening capacity. This will help the team assess screening procedures, staffing, and supplies to identify potential gaps that would be addressed before implementing the multicomponent strategies. As part of this process, we will review standard operating procedures (SOPs) for the screening process, data entry in clinic tracking systems, and referrals for supplemental and diagnostic testing and cancer treatment. To evaluate the implementation of the SOPs and identify potential bottlenecks, we will conduct a pilot study by offering cancer screening and follow-up services to 10 eligible women from the catchment area of 1 participating clinic in each county. These 30 women will be selected from communities not included in this study, and lessons learned will be used to finalize the SOPs and improve clinic data quality. We will host a 1-day training in each county for physicians and nurses—2 health care providers per clinic, to strengthen workforce capacity on practice facilitation to deliver high-quality breast and cervical cancer screenings, improve patient communication, and reduce stigmatizing behavior [58]. The clinic team will receive training using existing training materials on the following topics [59-61]: (1) running effective meetings and supporting team discussion, (2) developing a formal process to seek updates from C3Link CHWs and clinic teams to improve patient communication, (3) reviewing screening and referral data with the team, and (4) using the Plan-Do-Study-Act method [61] to address any gaps in implementing the SOPs.

### Study Design and Sample Size Determination

The sample size was determined using standard parameters (*α*=.05, 2-sided tests), based on the primary end point and allowing for the detection of a 15 percentage point improvement in the primary end point, our minimum threshold to consider the C3Link package of strategies to be successful. For the enhanced standard-of-care arm, given the current low level of screening, we estimated the screening uptake for both cancers to be about 15% at the 24-month follow-up (end of intervention phase). With a sample size of 100 in each of the 9 communities in the trial arms (for a total of 2700 women, and each woman will select 1 family member or support person), we will be able to detect a 15% difference with over 80% power, even after accounting for up to 20% attrition at 24 months. We selected a screening uptake of at least 30% in either the C3Link Core or Plus arm on the basis of prior study results [62,63]. We estimate that the interclass correlation coefficient would be in the range of 0.03 to 0.05 because interclass correlation coefficients for binary data are typically quite small, especially when screening uptake is very low [64]. Furthermore, we anticipate that the C3Link Plus arm would achieve a higher uptake than the C3Link Core arm, and we would be able to detect any difference of 15 percentage points between this study’s arms (ie, screening uptake of 15%, 30%, and 45% in the enhanced standard-of-care, C3Link Core, and C3Link Plus arms, respectively) with over 90% power. In each community, we will select study participants, 1 woman per household, using the Kish method [65], with eligibility remaining the same as previously stated. We will oversample by 10% to account for participants who cannot be contacted, refuse to participate, or are no longer eligible. The C3Link study cluster randomization is presented in Figure 2.

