### Recruitment

The 3 communities per study clinic will be randomly assigned to one of the following study arms: C3Link Core, C3Link Plus, or enhanced standard of care. Trained study data collectors and study CHWs will visit households in the selected communities with the help of county CHWs (promoters). They will visit households in selected communities and enroll eligible women. Women will be eligible to participate if they are 30 to 55 years of age to capture most cases of persistent HPV infections (lower age limit) and those within the peak age groups of breast cancer incidence rate in Kenya (higher age limit). These women will be due to receive both breast and cervical cancer screening during this study’s intervention phase based on Kenyan guideline recommendations, not experiencing breast or cervical cancer symptoms, not pregnant, fluent in a study language (English, Kiswahili, Kamba, Kalenjin, and Kikuyu), and have plans to remain in the community for at least 2 years. We will include women who meet the inclusion criteria (1 per household using the Kish method) [65].

The study CHWs will administer a short survey to all women to assess eligibility for this study. The data collectors will administer the baseline survey to women who will give voluntary informed consent to participate. Each enrolled woman will be allowed to select a support person (spouse or community member) older than 18 years of age—the legal age for consent for health research in Kenya, with help from their CHW if needed. Selecting a support person will be voluntary. Study CHWs will administer a support person eligibility checklist tool before data collectors administer the support person baseline survey to those who give voluntary informed consent.

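### The claim of over 90% power for any 15-point difference between arms is not met over the plan's own ICC range; Core 30% versus Plus 45% has about 76% to 90%

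*Protocol article*

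**What the plan says.** All the relevant text is in the protocol article, Methods, Study Design and Sample Size Determination, except the allocation, which is under Recruitment.

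- **Design inputs.** Alpha is 0.05, two-sided. The size is given as "With a sample size of 100 in each of the 9 communities in the trial arms", for 2700 women in total. The correlation "coefficient would be in the range of 0.03 to 0.05". Recruitment gives the allocation: "The 3 communities per study clinic will be randomly assigned to one of the following study arms", so each arm has 9 communities, one per clinic.
- **First power statement.** With control uptake of about 15% at 24 months and at least 30% in an active arm, the article says "we will be able to detect a 15% difference with over 80% power, even after accounting for up to 20% attrition at 24 months".
- **Second power statement.** It then says "we would be able to detect any difference of 15 percentage points" between the arms, lists 15%, 30% and 45% as the rates, and attaches them to the arms "in the enhanced standard-of-care, C3Link Core, and C3Link Plus arms, respectively) with over 90% power". The Core versus Plus comparison (30% versus 45%) is therefore explicitly covered.

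**The concern.** For a fixed gap, fixed cluster numbers and a fixed ICC, the power to compare two proportions falls as the proportions move towards 50%, because the binomial variance grows. The summed variance is 0.15×0.85 + 0.30×0.70 = 0.3375 for 15% versus 30%, and 0.30×0.70 + 0.45×0.55 = 0.4575 for 30% versus 45%. Core versus Plus is thus the harder of the two 15-point comparisons, and it deserved a check before a common figure of over 90% was attached to both.

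Plus versus Core shows whether the more resource-intensive individual strategies add anything to group education. It is part of the first hypothesis (Hypothesis Testing), and the Discussion says that the incremental results are meant to guide policy. A reader facing a null Plus versus Core result would take the chance of missing a true 15-point gain to be below 10%. At the top of the plan's ICC range it is about 24%.

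**Working it through.** **Inputs, all from the article.** Communities per arm: 9. Women per community: m = 100 enrolled, or m = 80 after 20% attrition (720 analysed per arm). ICC: 0.03 to 0.05. Two-sided alpha: 0.05, critical value 1.96. Difference: 0.15.

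**Formulas.**
- Design effect: DE = 1 + (m − 1) × ICC
- Effective number per arm: n_eff = 9m / DE
- SE = √[(p1(1 − p1) + p2(1 − p2)) / n_eff]
- Power = Φ(0.15/SE − 1.96)

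**Step 1: the first statement (over 80%, 15% versus 30%, after attrition).** m = 80, summed variance 0.3375.

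| ICC | DE | n_eff | SE | 0.15/SE | Power |
|---|---|---|---|---|---|
| 0.03 | 3.37 | 213.6 | 0.0397 | 3.774 | 96.5% |
| 0.04 | 4.16 | 173.1 | 0.0442 | 3.397 | 92.5% |
| 0.05 | 4.95 | 145.5 | 0.0482 | 3.114 | 87.6% |

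Over 80% is reproduced throughout. Over 90% fails at ICC 0.05 even for this easier pair. Without attrition (m = 100) the values are 97.3%, 93.6% and 88.8%, so it fails at ICC 0.05 there as well.

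**Step 2: the second statement (over 90%, 30% versus 45%), after attrition.** m = 80, summed variance 0.4575.

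| ICC | DE | n_eff | SE | 0.15/SE | Power |
|---|---|---|---|---|---|
| 0.03 | 3.37 | 213.6 | 0.0463 | 3.242 | 90.0% |
| 0.04 | 4.16 | 173.1 | 0.0514 | 2.918 | 83.1% |
| 0.05 | 4.95 | 145.5 | 0.0561 | 2.675 | 76.3% |

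**Step 3: the same pair without attrition.** m = 100.

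| ICC | DE | n_eff | SE | 0.15/SE | Power |
|---|---|---|---|---|---|
| 0.03 | 3.97 | 226.7 | 0.0449 | 3.339 | 91.6% |
| 0.04 | 4.96 | 181.5 | 0.0502 | 2.987 | 84.8% |
| 0.05 | 5.95 | 151.3 | 0.0550 | 2.727 | 77.9% |

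This is the reading most favourable to the text, and it exceeds 90% only at ICC 0.03.

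**Step 4: sensitivity to the method, 30% versus 45%, ICC 0.03 to 0.05.**
- Pooled variance under the null: 89.6% to 75.5% with attrition, 91.2% to 77.1% without. On this formula, 90% requires an ICC below about 0.029 with attrition or 0.032 without.
- t reference with 16 df (18 communities less 2), with attrition: 86.0% to 70.9%. The matching range for 15% versus 30% is 94.3% to 83.2%.
- One-sided alpha of 0.05, which the plan does not use, with attrition: 94.3% to 84.4%.

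None of these exceeds 90% across the stated ICC range.

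**The case against.** **Attrition.** The 20% allowance is attached to the 80% sentence and is not repeated in the 90% sentence, which may refer to full enrolment. That is a fair reading. It makes the claim true at ICC 0.03 (91.6%), but not at 0.04 or 0.05.

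**Blocking by clinic.** One community per arm is drawn from each clinic, so an analysis that uses the clinic as a block could remove part of the between-community variance. If half of the ICC lay between clinics, power for 30% versus 45% after attrition would be about 93% to 98%. If a quarter did, it would be about 85% to 95%. These shares are assumptions: the article gives no split of the ICC and claims no gain from blocking in its power paragraph. The point does not rescue the figure, but it is a reason not to lead with the t-based 71%.

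**Global test.** A three-arm global test would have over 99.9% power. However, the sentence speaks of a 15-point difference between arms, which is a pairwise statement.

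**Three stronger readings are tempting and are not supported.**
- A reader might infer that the two power statements contradict each other, since the harder comparison carries the higher figure. Over 80% is only a lower bound, and the actual power for 15% versus 30% is 88% to 97% after attrition. The sentences are compatible as worded; only the recalculation shows the error.
- A reader might infer that success in either active arm, tested at an unadjusted 0.05, inflates the false-positive rate. The word 'either' occurs in a planning assumption about uptake, not in a success rule. Multiplicity and test order are commonly left to a statistical analysis plan, which is not shown here.
- A reader might infer that the trial is too small. The sample size was set for a 15-point gain over a 15% control rate, and the power stated for that comparison is confirmed.

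**Conclusion.** The figure is wrong as written. Over the stated ICC range, a 15-point difference between Core at 30% and Plus at 45% is detected with about 76% to 90% power after the planned attrition, and about 78% to 92% without it. The shortfall is not confined to that pair: 15% versus 30% also drops below 90% at ICC 0.05 (about 88% after attrition, 89% without).

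The type II error for Core versus Plus after attrition therefore runs from about 10% at ICC 0.03 to 24% at ICC 0.05; the 24% is the worst case, not the expected one.

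These results assume equal community sizes, a two-sided 0.05 for each comparison, a normal reference and no gain from clinic blocking. The claim of over 80% for 15% versus 30% stands.

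The sentence should be corrected because a null Plus versus Core result would be read against it. The error changes no sample size, estimate or analysis.

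**What to change.** In Study Design and Sample Size Determination, replace the closing claim of over 90% power with wording such as: after 20% attrition, power is about 76% (ICC 0.05) to 90% (ICC 0.03) for 30% versus 45%, and about 88% to 97% for 15% versus 30%. Optionally add that a t reference with 16 df and no gain from clinic blocking gives 71% to 86% and 83% to 94%. If the authors' figure relied on a gain from blocking, they should state the share of the ICC assumed to lie between clinics.

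The cost is one sentence and a less favourable stated figure. Recruitment ended in late 2024 and no extra participants are needed. The correction is best made before the 24-month analysis, planned for 2027, so that a null Plus versus Core result is read against the right figure.
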